### Pharmacist service

The on-site pharmacist will monitor the participants using the TCC-ADEPT dashboard which includes data from the digital technologies as well as daily uploaded clinical and medicine data. Where clinically significant changes are detected, the resident will be automatically flagged for the pharmacist to take appropriate action (eg, continue monitoring, perform a review or initiate multidisciplinary review).

### Sample size

A sample size of 30–50 participants is recommended for pilot and feasibility studies.^29^ The current study aims to recruit 30 participants from a 120-bed residential aged care facility.

### Outcomes and analysis

Study outcomes will be measured at 4-week, 8-week and 12-week postbaseline period. Health outcomes include number of medication adverse events and change in resident symptom score (ESAS); surrogate measure outcomes include change in physical activity and sleep; process measure outcomes include number of pharmacist recommendations provided, record of staff time spent during study implementation period and proportion of all pharmacists’ recommendations to GPs and aged care staff that are implemented.

#### Process evaluation to assess the feasibility of the pharmacist service

A mixed methods evaluation, applying the RE-AIM evaluation framework^30^ will be performed to assess the feasibility of the pharmacist service. Descriptive statistics will be employed to report demographic characteristics and health information obtained from the Resident Care Assessment Record.

To determine *reach*, the number and proportion of eligible residents who were willing to participate in the study will be calculated. Information that will be collected include number of residents approached by the study staff or pharmacist and provided with the study information, number of residents who meet the inclusion criteria, number of residents who provided consent and number of participants who completed the 12-week study.

To determine *effectiveness*, changes in resident symptom score predigital and postdigital pharmacist service, as measured using the ESAS, will be assessed. Changes in medication use will be assessed, including changes to sedative and anticholinergic load predigital and postdigital pharmacist service. Changes in 24-hour movement behaviour, as measured using the activity tracker, will be assessed predigital and postdigital pharmacist service. The number of adverse events including falls (both injurious and non-injurious), fractures, delirium, faecal impaction, hospitalisation or emergency department presentation due to adverse medication events and medication incidents will be assessed. The number of adverse events experienced by residents within the 12-week predigital pharmacist service versus number of adverse events experienced during the 12-week digital pharmacist service period will be compared. Pre-post paired t-test or Wilcoxon test will be used for continuous data and McNemar’s tests for categorical variables.

To assess service *adoption*, the number and proportion of organisation staff invited, that agreed to participate, will be calculated.

To assess *implementation*, the number and types of pharmacist recommendations will be recorded and evaluated. In addition, the proportion of recommendations made by the pharmacist will be compared with the number of recommendations accepted, to determine the acceptability of the digital pharmacist service by the GPs and aged care staff. Semi-structured interviews or focus groups will be conducted with the project pharmacist, GPs, aged care staff, residents and family members to understand their views of the digital pharmacist service, including facilitators and barriers to its delivery. An analysis will be undertaken of the costs associated with implementing the ADEPT-assisted pharmacist service. The resource use associated with the implementation of the ADEPT pharmacist service, including staff (aged care and health professionals) time, equipment and resources will be recorded by trial staff prospectively. Changes in pharmacist time spent reviewing residents will be measured using pharmacist’s record of amount of time spent reviewing medications for residents, generating recommendations and communicating with staff, GPs and residents. Resources will be valued using appropriate unit costs drawn from organisational finance data, relevant published employment awards,^31^ the Medicare Benefits Schedule (list of medical services that the Australian Government provides a rebate to assist with costs) and the Pharmaceutical Benefits Scheme (Australian Government programme that subsidises costs of prescription medications).^32 33^ Where valuations are unable to be obtained from published data, we will value using market rates, using the average cost from three suppliers. Prices will be updated to the current year using the Consumer Price Index.^34^ A budget impact analysis will be conducted, extrapolating the within-study assessment of costs to a wider population level.

To assess *maintenance*, interviews with senior management at the aged care facility will be conducted to understand intention to continue to implement the service poststudy funding, and whether the service aligns to the facility’s mission or sustainability of business model. The capacity of the aged care organisation to implement the service (beyond the feasibility study) to identify and negate potential medicine-induced harms will be explored.

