**Methods and analysis:**

Thirty residents will be recruited from an aged care facility in South Australia. The study will be conducted in two phases. In phase I, the study team will work with aged care software providers and developers of digital technologies (a wearable activity tracker and a sleep tracking sensor) to gather physical activity and sleep data, as well as medication and clinical data from the electronic medication management system and aged care clinical software. Data will be centralised into a cloud-based monitoring platform (TeleClinical Care (TCC)). The TCC will be used to create dashboards that will include longitudinal visualisations of changes in residents’ health, function and medicine use over time. In phase II, the on-site pharmacist will use the centralised TCC platform to monitor each resident’s medicine, clinical, physical activity and sleep data to identify signs of medicine-induced harms over a 12-week period.

A mixed methods process evaluation applying the RE-AIM (Reach, Effectiveness, Adoption, Implementation, Maintenance) evaluation framework will be used to assess the feasibility of the service. Outcome measures include service reach, changes in resident symptom scores (measured using the Edmonton Symptom Assessment System), number of medication adverse events detected, changes in physical activity and sleep, number of pharmacist recommendations provided, cost analysis and proportion of all pharmacists’ recommendations implemented at 4-week, 8-week and 12-week postbaseline period.

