### Baseline data collection

Once written consent is obtained, study staff will collect baseline data from the Resident Care Assessment Record held electronically in Leecare^21^ and Medi-Map^22^ software, which contains demographic details, comorbidities, medicine use, falls history and care provided within the aged care facility. Study staff will administer the ESAS^17^ and the Montreal Cognitive Assessment (MoCA)^23^ at baseline. An observational logbook or diary will be kept to record information not collected in the existing data fields. Table 1 indicates data collected at each data collection time points.

**Table 1 T1:** Data collection schedule

Variable	Description	Data source	Data collection time points			
			Baseline	4 weeks	8 weeks	12 weeks
Demographic	Age, gender	Leecare	✓			
Medical conditions	Diagnosis of medical condition	Leecare	✓	✓	✓	✓
Medications*	Name, strength, dose, frequency of medicine administration	Medi-Map	✓	✓	✓	✓
Nutritional status	Swallowing status	Leecare	✓			✓
Functional ability	Mobilisation status	Leecare	✓			✓
Cognitive function	Montreal Cognitive Assessment	Leecare	✓			✓
Falls history	Number of falls and related health outcomes	Leecare	✓			✓
Vital signs	Height, weight, blood pressure (systolic and diastolic), respirations, pulse, BGL, SpO_2_	Leecare	✓	✓	✓	✓
Pain	PainChek score severity across six domains	Leecare	✓	✓	✓	✓
Residential Medication Management Review (RMMR)	Dates of RMMR provision will be recorded	On-site aged care pharmacist	✓	✓	✓	✓
Physical activity	Time spent in light, moderate, vigorous-intensity activity	Fibion SENS device	✓	✓	✓	✓
Sleep	Movements during sleep, durations of light, deep and REM sleep	Fibion Emfit device	✓	✓	✓	✓
Edmonton Symptom Assessment Scale	Severity across 10 symptoms	Participant or third-party informant review	✓	✓	✓	✓
Adverse events	For example, falls, fracture, delirium, faecal impaction, incontinence	Leecare, pharmacists, aged care staff, residents	✓	✓	✓	✓
Incidents	Medication incidents will be recorded including date/time and severity	Leecare, pharmacists, aged care staff, residents	✓	✓	✓	✓
Ambulance call-outs	Date and reasons will be recorded	Leecare, pharmacists, aged care staff, residents	✓	✓	✓	✓
Hospital visits	Date and reason of emergency department visits or hospital admission will be recorded	Leecare, pharmacists, aged care staff, residents	✓	✓	✓	✓
All-cause mortality	Any deaths in the 12-week study period will be recorded	Aged care staff		✓	✓	✓

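### The adverse event outcome is defined in two ways, and its medicine-attributed part would be judged on different evidence before and during the service

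*Protocol article*

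**What the plan says.** The outcome appears under two descriptions.

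- **Medicine-attributed.** The abstract lists "number of medication adverse events detected" among the outcome measures. The section on outcomes and analysis says "Health outcomes include number of medication adverse events".
- **Mixed list.** The process evaluation section, under effectiveness, opens its list with falls, with or without injury, and continues "fractures, delirium, faecal impaction, hospitalisation or emergency department presentation due to adverse medication events and medication incidents will be assessed". The aims at the end of the Introduction give the same list. The process evaluation then compares the number of adverse events in the 12 weeks before the digital service with the number in its 12 weeks. It names paired t or Wilcoxon tests for continuous data and McNemar's test for categorical data.

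Table 1 is organised differently again. Its adverse event row reads "For example, falls, fracture, delirium, faecal impaction, incontinence", with no causal condition and with incontinence, which the effectiveness list omits. Medication incidents have their own row. So do hospital visits: "Date and reason of emergency department visits or hospital admission will be recorded", not restricted to medicine-related ones.

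On causality, the section on identifying triggers for review has the on-site pharmacist decide whether harm is medicine-induced from device, clinical and medicine data on the dashboard. Phase II provides two weeks of device data before the pharmacist service starts.

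**The concern.** A pre-post comparison of counts needs the same definition, applied with the same evidence, in both periods. Here the definition changes between sections, and at least one component (hospital and emergency contact) passes through a causal judgement. If that judgement is made with the dashboard during the service and without it beforehand, the same admission could be called medicine-related in one period and not in the other.

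The direction of any bias is awkward too. The study hypothesises better detection of medicine harms, yet its risks section anticipates fewer adverse events. Better attribution would push the recorded number up while real benefit would push it down, and the comparison could not separate the two.

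A secondary matter is that the list contains events that can follow from one another, so what one unit of the count represents is unclear.

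**Working it through.** **1. Definitions side by side**

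| Place | Falls, fractures, delirium, faecal impaction | Hospital or emergency contact | Medication incidents |
|---|---|---|---|
| Abstract; Outcomes and analysis | Only if medication adverse events | Only if medication adverse events | Not mentioned |
| Aims; Process evaluation | No clear causal condition | Only if medicine-related | Counted item, or a cause of the contact |
| Table 1 | No causal condition; incontinence added | All, with date and reason | Separate row |

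The three rows do not define the same quantity.

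**2. Two readings of the causal phrase.** If it governs only hospital and emergency contacts, all-cause and attributed events sit in one number. If it governs the whole list, every component needs a causal judgement in both periods. Either way some part of the count is attributed.

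**3. What attribution does to the comparison.** Let H be the number of hospital and emergency contacts, the same in both periods, and let a1 and a2 be the shares judged medicine-related before and during the service. The recorded numbers are H × a1 and H × a2, so their ratio is a2/a1. It departs from 1 whenever the shares differ, with no change in harm. The document gives neither share. On evidence: if the two weeks of baseline device data fall inside the 12 pre-service weeks (an assumption), 12 − 2 = 10 of those weeks have no device data.

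**4. Scale of the count.** No expected count is stated, and the sample size of 30 rests on a general recommendation for feasibility studies, so there is no planned figure to reproduce. The Introduction gives about one in five residents with an adverse medicine event per month in Australia, and up to 27 events per 100 residents per month. Treating the first as an event rate (an assumption, since it is a proportion of persons):

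- 12 weeks = 84 / 30.44 = 2.76 months
- 30 × 0.20 × 2.76 = 16.6 events per period
- 30 × 0.27 × 2.76 = 22.4 events per period

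These are rates of medicine-related events. An all-cause list would have its own rate, which is not given.

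**5. Overlap, if components were summed.** A fall alone gives 1 entry, a fall with a qualifying visit 2, and a fall with a fracture and a qualifying visit 3. A linked incident would make 4, but only if incidents are a counted item. If a share q of episodes gives m entries and the rest give 1, the count is multiplied by 1 − q + q × m. With m = 3 and q assumed between 5% and 30%:

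- q = 0.05: 0.95 + 0.15 = 1.10, or +10%
- q = 0.30: 0.70 + 0.90 = 1.60, or +60%

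This raises the level in both periods. If q and m are equal across periods the multiplier cancels in the pre-post ratio. What remains is extra variability: taking episodes as Poisson, the variance-to-mean ratio (1 − q + q × m²)/(1 − q + q × m) is 1.40/1.10 = 1.27 at q = 0.05 and 3.40/1.60 = 2.12 at q = 0.30, against 1 without overlap. The shares are assumptions, so these are illustrations only.

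**The case against.** A reader might infer that the plan adds linked events and error reports together, that an injurious fall counts three or more times, and that the result is therefore not a count of harms. The document does not support this.

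- It never says that components are summed or that linked events count separately. A counting rule is detail an article may leave to the full protocol or analysis plan.
- Table 1 keeps incidents in their own row and has a falls row that includes related health outcomes, so some linkage is planned.
- The phrase ending in medication incidents can be read as naming a cause of hospital contact rather than a further counted item.
- Three entries need a fall with at least two further listed events, and most listed items are harms.
- A McNemar comparison of residents with any event would be unaffected by repeat counting.

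These points stand, and they confine the overlap argument to a possibility.

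Two further objections stand only in part. The causal phrase may govern the whole list, which would bring it closer to the outcomes section. But that reading extends attribution to every component, and so widens the difference in evidence between periods. It is also fair that the dashboard section describes how the pharmacist identifies harm and does not name an adjudicator for this outcome; Table 1 draws events from care records, pharmacists, staff and residents. But no other route to a causal judgement is described, and a McNemar analysis of attributed events would depend on that judgement too.

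**Conclusion.** The concern holds in a limited form. The article defines the adverse event outcome inconsistently, as medicine-attributed in two places and as a mixed list in two others, with a third version in Table 1. Because the only described means of attributing harm to medicines is absent for the pre-service 12 weeks, the attributed part of the comparison may reflect a change in judgement rather than in harm. This assumes that attribution follows the described route; the document does not say otherwise.

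The size of the bias cannot be derived, because neither attribution share nor the proportion of linked episodes is given. The base is small, roughly 17 to 22 events per period at the quoted rates, so a few reclassified contacts would be visible in the result. Overlap between listed events is possible but not shown to distort the pre-post difference. This is one of several outcomes in a 30-resident feasibility study, so the point is worth correcting but does not undermine the study.

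**What to change.** 1. Use one event list and one name for the outcome in the abstract, the aims, Table 1, the outcomes section and the process evaluation. Decide whether incontinence belongs.
2. Base the pre-post comparison on all-cause events, reported separately by type: falls, fractures, delirium, faecal impaction, and emergency visits or admissions. Reporting by type also removes the question of how linked events add up.
3. Report medication incidents on their own line, as Table 1 already records them.
4. Keep the pharmacist's attribution to medicines as a descriptive outcome of the service period, outside the before-and-after comparison.

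The cost is mainly wording. Table 1 already records hospital and emergency visits with date and reason, and has a row for the other event types. The real downside is that all-cause counts are less specific to medicine harm, and counts by type will be smaller than a single total.

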## Introduction

Approximately 8% of adults in Australia aged 65 years and older reside in aged-care facilities (nursing home),^1^ with up to 63% receiving nine or more regular medications.^1^ Medicine-related problems contribute to an estimated 250 000 hospital admissions in Australia every year, with an estimated annual cost of US$1.4 billion.^2^ Medicine-related harms are of significant concern in residential aged care, with up to 27 adverse medicine events occurring per 100 residents per month.^3–5^ In Australia, about one in five persons living in residential aged care experience an adverse medicine event every month; of which 83% were potentially preventable.^6^ Despite the significant medicine-related harms, most Australian residential aged care facilities have limited capacity to provide clinical pharmacy services; existing services are limited to government-funded residential medication management review (comprehensive medication reviews performed by accredited pharmacists in residential aged care) and quality use of medicine services.^7^

The Australian Government, recognising the significance of medicine-related problems in aged care, committed US$350 million to improve medication safety in residential aged care through funding for pharmacists.^8^ The government investment presents new opportunities for pharmacists to review residents for signs and symptoms of medicine harms more frequently. The present study builds on our recent randomised controlled trial which investigated the effectiveness of ongoing pharmacist assessments compared with usual care in reducing medicine-induced deterioration, frailty and adverse events across 39 residential aged care facilities in Australia.^9 10^ Our study showed that one in five residents experienced a preventable adverse event (eg, falls, fractures) every month due to medication use.^9^ The pharmacists identified and resolved medicine-related harms and served as an advocate for residents. Furthermore, significant differences in change in cognition from baseline were observed between intervention and control groups.^9^ The service ensured pharmacist engagement with residents, rather than just reviewing medicines, which enabled the advocacy.^11^

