### Cohort selection

Residents will be considered eligible to participate if they are a permanent resident living in the designated residential aged care facility. Exclusion criteria include receiving palliative or respite care.

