### Phase II

The pre-post feasibility study will be conducted over 12 weeks. The study will be reported according to the Consolidated Standards of Reporting Trials checklist for pilot and feasibility trials.^28^ The sleep sensor (Fibion Emfit)^19^ will be installed in the rooms of all enrolled and consenting residents, and study staff will provide residents with an activity tracker (Fibion SENS).^18^ Two weeks of baseline data will be collected from these technologies prior to the start of the pharmacist service.

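### The before-after count of adverse events is not like with like: the 12 pre-service weeks largely exclude terminal decline by the entry rule, while the 12 service weeks can include it, and raw counts can be shifted in either direction

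*Protocol article*

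**What the plan says.** In the process evaluation section, under effectiveness, the protocol article compares "The number of adverse events experienced by residents within the 12-week predigital pharmacist service versus number of adverse events experienced" during the 12-week service. The events include falls, fractures, delirium, faecal impaction, hospital or emergency presentation due to adverse medication events, and medication incidents. The tests are fixed in the same paragraph: "Pre-post paired t-test or Wilcoxon test will be used for continuous data and McNemar’s tests for categorical variables". There is no concurrent control.

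Three other places bear on who contributes to each period:

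- Cohort selection: "Residents will be considered eligible to participate if they are a permanent resident living in the designated residential aged care facility". It continues: "Exclusion criteria include receiving palliative or respite care".
- Table 1, all-cause mortality: "Any deaths in the 12-week study period will be recorded". This row is ticked at 4, 8 and 12 weeks and not at baseline.
- Phase II: "Two weeks of baseline data will be collected from these technologies prior to the start of the pharmacist service". No other prospective collection before the service is described.

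Under reach, the article also counts the "number of participants who completed the 12-week study", so it expects some incomplete follow-up. It does not say how residents without complete follow-up enter the event comparison.

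**The concern.** Only two weeks of prospective pre-service collection are described, so most or all of the 12-week pre-service count must come from records that predate enrolment. This is an inference; the article does not call it a look-back. A resident who died or became palliative in those weeks is not in the cohort, and that resident's events are not in the pre-service count. A resident who does the same in the service weeks is in the cohort, and the events count up to death.

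Falls, delirium and emergency presentations may cluster before death. If they do, the service period carries a load that the entry rule has largely removed from the pre-service period. Dividing by time at risk does not cure this, because the difference lies in who was allowed to contribute.

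The comparison carries the effectiveness label and significance tests, and the Risks section looks forward to fewer adverse events as a benefit. A reader may take a rise, a fall or no change as a signal about the service when part of it comes from the entry rule and from lost follow-up.

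**Working it through.** The article states no expected pre-service or service count, so there is no figure of its own to reproduce. The check asks what service/pre ratio is expected when the service has no effect.

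**Inputs from the article**

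- Event rate, upper: "up to 27 adverse medicine events occurring per 100 residents per month" (Introduction).
- Event rate, lower: the Introduction's figure of about one resident in five per month, read as 20 events per 100 residents per month.
- 30 participants; two periods of 12 weeks (84 days).

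**Assumptions not in the article**

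- Annual mortality m = 20% or 35%, with constant hazard.
- Event rate multiplied by R in the last w = 4 or 8 weeks of life, with R from 1 to 6.
- Palliative status recognised p = 2 or 4 weeks before death. A resident within p weeks of death at entry is excluded.
- The pre-service period ends at enrolment.

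**Expected events and chance variation**

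- 30 × 0.20 × 84/30.4 = 16.6 and 30 × 0.27 × 84/30.4 = 22.4 events per period.
- Poisson SD of the difference between two such counts: √(2 × 16.6) = 5.8 and √(2 × 22.4) = 6.7.

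**Expected deaths in the service weeks**

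- Weekly hazard h = −ln(1 − m)/52 = 0.00429 or 0.00828.
- Ignoring the palliative exclusion: 30 × (1 − exp(−12h)) = 1.5 or 2.8 deaths.
- With it: 30 × (1 − exp(−(12 − p)h)), which runs from 1.0 (m = 20%, p = 4) to 2.4 (m = 35%, p = 2).

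**Ratio with no service effect**

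Let E be the mean weeks alive in the service period, T the mean terminal weeks within it, and P the mean terminal weeks in the pre-service period.

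- Raw ratio = [E + (R − 1)T] / [12 + (R − 1)P].
- Ratio per resident-day = raw ratio × 12/E.

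One setting in full (m = 35%, w = 8, p = 4): E = 11.741, T = 0.690, P = 0.0655.

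- R = 1: 11.741/12 = 0.98
- R = 2: 12.431/12.066 = 1.03
- R = 3: 13.121/12.131 = 1.08
- R = 6: 15.191/12.328 = 1.23; per resident-day 1.23 × 12/11.741 = 1.26

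All eight settings of m, w and p:

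| R | Raw counts, all residents | Per resident-day, all residents | Counts, alive at week 12 | Counts, alive and not palliative at week 12 |
|---|---|---|---|---|
| 1 | 0.97-0.99 | 1.00 | 1.00 | 1.00 |
| 2 | 0.995-1.03 | 1.01-1.05 | 1.00-1.02 | 1.00-1.01 |
| 3 | 1.01-1.08 | 1.03-1.11 | 1.01-1.04 | 1.00-1.02 |
| 6 | 1.06-1.23 | 1.07-1.26 | 1.01-1.11 | 1.00-1.06 |

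**Where the sign of the raw count turns**

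The raw ratio equals 1 when R − 1 = (12 − E)/(T − P). For the setting above this is 0.259/0.6245 = 0.41, so R = 1.4. For m = 35%, w = 4, p = 2 (E = 11.597, T = 0.362, P = 0.0165) it is 0.403/0.3455 = 1.17, so R = 2.2. Below that point, lost time outweighs terminal decline and the raw count falls.

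**A second set of assumptions**

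With 12-week mortality of 3-10%, R from 1 to 3, the same windows, and the palliative exclusion either fully effective or removing no one, the raw ratio runs from 0.95 to 1.085.

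**In events**

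The largest shift is 0.23 × 22.4 = 5.2 events. At R = 3 it is at most 0.08 × 22.4 = 1.8. At R = 1 the raw count falls by at most 0.03 × 22.4 = 0.7.

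**The case against.** A reader might infer that adverse events must appear to rise under the service, or that the comparison is biased against the service whatever the circumstances. The documents do not support this. The article compares numbers of events, and a death removes service time as well as adding terminal events. Where event rates do not rise, or rise only modestly, before death, the raw count falls or hardly changes. Nothing in the article fixes mortality, the length of terminal decline or its rate ratio. The figure of 1.23 needs the extreme of every assumption at once, and nothing shows that adverse medicine events rise sixfold before death.

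Four further objections carry weight:

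- The shift is small beside chance. Even the extreme case is below one SD of the difference. Failure to see a real reduction would owe more to 30 participants than to this mechanism.
- The article does not fix where the pre-service period ends. If it ends at service start, up to two of its weeks follow enrolment, and with R between 3 and 6 the raw range becomes 1.00-1.20.
- If only 12-week completers enter the paired tests, most of the effect goes: 1.01-1.11 for R between 3 and 6. The choice of analysis set may stand in a fuller document that is not shown.
- This is a feasibility study without a control group and cannot carry a causal claim in any case.

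These points limit direction, size and weight. They leave the asymmetry standing. The windows, the contrast and the entry rule are stated choices, not details left to another document, and neither a rate per resident-day nor restriction to survivors alone removes the difference.

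**Conclusion.** The stated comparison is not like with like. Apart from a possible two-week run-in, the pre-service weeks are conditioned on being alive and not palliative at their end, and the service weeks are not. With no service effect, events per resident-day are biased upward if event rates rise before death (1.01-1.05 at a terminal rate ratio of 2, up to 1.26 at 6). Raw counts may be biased either way: about 0.97-1.03 at a ratio of 1-2, 1.01-1.08 at 3, and up to 1.23 at 6. The shift is at most about 5 events, against a chance SD of about 6.

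The asymmetry rests on the article's text and on the inference that the pre-service count is largely a look-back. The sizes rest on assumed mortality, terminal window, rate ratio and timing of palliative recognition. For a feasibility study of 30 residents this is a cheap improvement in what the comparison can support. It does not invalidate the study.

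**What to change.** In the effectiveness paragraph of the process evaluation section:

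1. Keep the all-resident comparison, and report it as events per resident-day at risk in both periods.
2. Add beside it the pre-service and service counts in residents who are alive and not in palliative care at week 12, so that the entry condition holds at the end of both periods.
3. List separately the service-period events of residents who die or become palliative.
4. State that the all-resident rate comparison can be biased towards more events under the service, that raw counts may be biased in either direction, and that the contrast is descriptive.

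The cost is one table, one short listing and a caveat. Deaths and events are already in Table 1. Palliative status during the service weeks is not named there, so its date would have to be added to the record extraction.

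The downside is that the restricted table conditions on survival and leaves out fatal medicine harms. It must stand beside the all-resident comparison and not replace it. It also does not remove the bias wholly: under the assumptions above, a ratio of up to 1.06 remains at a terminal rate ratio of 6.
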